## Alternative hypothesis

The difference in the cure rates between 2 groups obtained during the treatment of patients in the meningo-encephalitic phase is less than or equal to 10%.

If the observed difference in cure rates between the 2 groups is less than 10%, the null hypothesis will be rejected and the two treatments will be considered equivalent. The risk of error will then be 5% (alpha error) because if the difference in actual cure rates between the 2 treatments is greater than 10%, there is a 95% chance of demonstrating it (alpha error). Conversely, if the observed difference in the observed cure rates between the two groups is greater than 10%, the null hypothesis will not be rejected and the 2 treatments will be considered different, at a beta error set at 20%. The allocation ratio will be uniform (1 patient in group A to 1 patient in group B to 1 patient in group C).

Assuming a 95% cure rate, a maximum difference in cure rates between the groups of 10%, an identical drop-out rate in the 3 groups, an alpha error of 5% (one-sided test) and a power of 80%, this yields a sample size of 130 patients to be included in each group, i.e. 390 patients in the study. Allowing for a 10% drop-out rate, a final figure of 145 patients per group is obtained, i.e. 435 patients in total.

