## Multivariate analysis

Certain clinical and laboratory variables might be confounding factors, which must be taken into account during the analysis. Cox’s model (proportional hazard) will be used to obtain an estimate of the relative risk adjusted for these variables.

In an equivalence study, the point of interest is the difference observed between the two groups, assuming a 90% confidence interval (or an upper limit of 95%) around this difference (with a one-tailed test):

- If the upper limit is above 10%, the null hypothesis that there is a difference between the 2 groups cannot be rejected. If B is compared with A, it will be concluded that B is superior to A (at the 20% level).
- If the upper limit is below 0%, it will be concluded that A is superior to B (at the 20% level).
- Finally, if the upper limit is between 0 and 10%, the null hypothesis may be rejected and the alternative hypothesis accepted that the 2 groups A and B are equivalent (at the 5% level).

In the same way, for the analysis of survival, a 90% confidence interval (or an upper limit of 95%) is set around the relative hazard:

- If the upper limit is above a relative hazard of 1.12 (0.95/0.85) (i.e. 1.12 times more risk of treatment failure during the 24 months following treatment in one group than in the other), the null hypothesis that there is a difference between the 2 groups cannot be rejected.
- If the upper limit is below 1.0, it will be concluded that A is superior to B (at the 20% level).
- Finally, if the upper limit is between 1.0 and 1.12, the null hypothesis may be rejected and the alternative hypothesis accepted that the two groups A and B are equivalent (at the 5% level).

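### The survival equivalence margin of 1.12 is a ratio of cure proportions mislabelled as a hazard ratio of failure, so the rule can almost never conclude equivalence

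*Protocol*

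**What the plan says.** The sample-size section of the protocol (3.3, Alternative hypothesis) fixes the margin on the difference scale: "Assuming a 95% cure rate, a maximum difference in cure rates between the groups of 10" per cent, so the limiting comparison is 95% against 85% cure. It continues: "an alpha error of 5% (one-sided test) and a power of 80%, this yields a sample size of 130 patients to be included in each" of the three arms. The enrolment target follows: "Allowing for a 10% drop-out rate, a final figure of 145 patients per group is obtained". Allocation is equal across the three arms.

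Section 3.8, Survival analysis, makes time to parasitic recurrence over 24 months the third outcome, to be analysed by Kaplan-Meier curves and the log-rank test. Under Multivariate analysis a Cox "model (proportional hazard) will be used to obtain an estimate of the relative risk adjusted for these variables". After the decision rule for the difference in proportions, the same heading carries the approach over to survival: "for the analysis of survival, a 90% confidence interval (or an upper limit of 95%) is set around the relative hazard". The limit is then given as "If the upper limit is above a relative hazard of 1.12 (0.95/0.85) (i.e. 1.12 times more risk of treatment failure" over the 24 months. Equivalence is accepted "if the upper limit is between 1.0 and 1.12, the null hypothesis may be rejected". An upper limit below 1.0 is read as superiority of A.

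**The concern.** The bracket shows where 1.12 comes from: it is the assumed cure proportion divided by the lowest tolerable cure proportion. A hazard ratio in this analysis compares rates of failure, and the protocol's own gloss calls 1.12 a multiple of failure risk. When failure is rare, the ratio of two cure proportions is always close to 1, however different the failure risks are. The number has therefore been moved from one scale to another without conversion.

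At stake is a stated decision rule for a named outcome. If the limit is far tighter than the 10-point margin it is meant to express, and the expected number of failures is small, the rule will return an inconclusive result for nearly every pair of arms that really are equivalent.

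**Working it through.** **Inputs.** Reference cure 95%, margin 10 points, one-sided alpha 5%, power 80%, 130 per arm (145 enrolled): section 3.3. Limit 1.12, 90% confidence interval, Cox model: section 3.8. The one assumption beyond these is that failure may be higher than 5%. Section 1.2 reports about 25% failure after melarsoprol in Arua, the study site, so 25% is used as the upper end of the range.

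**1. Reproduce the protocol's figures.**
- Margin: 0.95/0.85 = 1.118, which rounds to 1.12.
- Sample size, comparing 95% with 85%, one-sided: n = [1.645·√(2·0.90·0.10) + 0.842·√(0.95·0.05 + 0.85·0.15)]² / 0.10² = 110.2, rounded up to 111. With continuity correction, (110.2/4)·[1 + √(1 + 4/(110.2·0.10))]² = 129.5, rounded up to 130. Then 130/0.90 = 144.4, rounded up to 145.

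Both reproduce, which confirms that 0.95 and 0.85 are cure proportions.

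**2. Put the margin on the failure scale.**
- Risk ratio: 0.15/0.05 = 3.0.
- Under proportional hazards S1 = S0^HR, so HR = ln(0.85)/ln(0.95) = 3.17.
- In reverse, HR 1.12 gives 0.95^1.12 = 0.944, i.e. 5.6% failure against 5%, a difference of about 0.6 points.

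**3. What the 1.12 rule does for one pair of arms that are truly identical.** Events d = 2·n·(failure proportion); SE of log HR = 2/√d; upper limit = HR·exp(1.645·SE); P(upper limit < m) = Φ(ln m/SE − 1.645). P(upper limit < 1.0) is 5%, so the window probability is this value minus 5%.

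| n per arm | Failure | Events | Upper limit if observed HR = 1.0 | Largest observed HR that passes 1.12 | P(upper limit < 1.12) | P(1.0 < upper limit < 1.12) |
|---|---|---|---|---|---|---|
| 130 | 5% | 13.0 | 2.49 | 0.45 | 7.5% | 2.5% |
| 145 | 5% | 14.5 | 2.37 | 0.47 | 7.7% | 2.7% |
| 130 | 25% | 65.0 | 1.50 | 0.75 | 11.7% | 6.7% |
| 145 | 25% | 72.5 | 1.47 | 0.76 | 12.3% | 7.3% |

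A Cox simulation (20,000 runs per sample size, true HR 1, 95% cure, censoring at 24 months) put the window probability at 2.2% for 130 per arm and 2.4% for 145.

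For 80% one-sided power against 1.12, 4·(1.645 + 0.842)²/(ln 1.12)² gives about 1,926 events per pair, or about 19,300 patients per arm at 5% failure.

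**4. What a converted hazard-ratio limit would do.** The equivalent of 10 points is ln(S0 − 0.10)/ln(S0), which depends on the reference cure rate S0: 3.17 at 95%, 2.12 at 90%, 1.77 at 85%, 1.50 at 75%. Against 3.17 with 13 events and identical arms, P(upper limit < 3.17) = Φ(1.153/0.555 − 1.645), about 67%; the like-for-like figure under 1.12 is 7.5%. In the simulation it was 63% (130 per arm) and 68% (145).

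**5. The difference scale for comparison.** At 5% failure and 130 per arm, SE = √(2·0.05·0.95/130) = 0.0270, and P(upper limit < 0.10) = Φ(0.10/0.0270 − 1.645), about 98%. At 25% failure, SE = √(2·0.25·0.75/130) = 0.0537, and the probability is about 59%.

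**The case against.** The scale error itself has no good defence. The bracket rules out a deliberately stricter margin, and nothing elsewhere in the protocol corrects it. The serious objections concern how far the point may be pushed, and they stand.

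- **Replacing 1.12 by 3.17.** A reader might infer that 3.17 is the correct margin. It equals 10 points only at 95% cure. Held fixed, it would tolerate 0.90^3.17 = 72% against 90% cure (18 points), 60% against 85% (25 points) and 40% against 75% (35 points). With about 25% failure after melarsoprol reported at the study site, and melarsoprol in two of the three arms, a hard-coded 3.17 could be far too lax. Any gain in power it shows at higher failure rates comes from that looser margin: at 10% failure (26 events), the matching limit of 2.12 gives only about 61%.
- **Contradiction with the primary result.** A reader might infer that the survival rule would contradict a finding of equivalence on the first outcome. For an upper limit above 1.12, the survival rule says only that the null cannot be rejected. An inconclusive third outcome is not strictly in conflict with an equivalent first one.
- **A two-sided limit.** Adding a lower bound of 1/3.17 would be a separate change. The rule is written on the upper limit alone, and the arithmetic error does not bear on that.
- **Importance.** This is the third outcome. Kaplan-Meier and log-rank are its named methods, and the 1.12 rule sits with the adjusted Cox analysis.

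**Conclusion.** The point holds. The limit of 1.12 is a ratio of cure proportions used as a hazard ratio and described as a multiple of failure risk. On the protocol's own assumptions the 10-point margin is a failure risk ratio of 3.0 and a hazard ratio of 3.17, whereas 1.12 stands for about 0.6 points.

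The consequence is that the rule can almost never conclude equivalence. Truly identical arms fall in the 1.0 to 1.12 window about 2.5% of the time at 5% failure, or about 7.5% if every upper limit below 1.12 is counted. At 25% failure the window probability is still only about 7%. These figures assume proportional hazards, the usual normal approximation for log HR and complete follow-up of 130 to 145 per arm. That 1.12 is too tight does not depend on the 95% figure, since the 10-point equivalent is 1.50 or more at every reference cure rate examined.

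It would be wrong to infer that the trial's size or main comparison is compromised: the primary analysis of the difference and the 130/145 per group do not use 1.12.

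**What to change.** Delete the 1.12 rule and its bracketed explanation. Judge survival equivalence by the 90% confidence interval for the difference between arms in 24-month Kaplan-Meier failure probability, against the same 10-point margin as the first outcome. Report the Cox hazard ratio with its confidence interval as supportive. This needs no conversion between scales and keeps the protocol's margin whatever the failure rate turns out to be, although power still falls if failure is well above 5%.

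If a hazard-ratio limit is kept, derive it as ln(S0 − 0.10)/ln(S0), state the reference cure rate S0 (3.17 at 95%, 2.12 at 90%, 1.77 at 85%, 1.50 at 75%), and state that power at 3.17 is only about 67% with 5% failure. Reaching 80% would take about 19 events per pair against the 13 expected.

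The cost is the wording of one paragraph, with no new data and no more patients. It should be done before outcomes are compared between arms, because a margin changed afterwards would look data-driven.

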## Follow-up duration

Patients included in the study will be monitored for 24 months after the end of treatment.

Laboratory tests (lumbar puncture, glandular puncture, QBC, haematology) and clinical examinations will be undertaken at the end of hospitalisation and 6, 12 and 24 months after the end of the treatment.

A network of community health workers will ensure the presence of the patients included in the study at the 3 scheduled follow-up visits as far as possible. In addition, the address of each patient included in the study will be noted at the time of admission. Anyone missing a follow-up visit will be sent a reminder 3 times.

Apart from this, the patient will be allowed to come at any time in the trypanosomiasis treatment centre throughout the follow-up period.

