**3.8. Analysis**

This will be an "intention-to-treat" analysis. The treatment groups will be compared pair-wise.

The first outcome variable is the proportion of therapeutic failures in each treatment group.

The second outcome variable is the proportion of side effects occurring in each group.

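### Protocol section 3.8 names a winning arm from confidence limits without fixing the scale or the reference arm; read in the only direction it gives, the survival rule names the arm that fails more

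*Protocol*

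**What the plan says.** Section 3.8, Multivariate analysis, gives two parallel sets of conclusions based on the upper limit of a 90% confidence interval.

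- **Difference between two groups.** For an upper limit above 10% the text says: "If B is compared with A, it will be concluded that B is superior to A (at the 20% level". An upper limit below 0% makes A superior. Between 0 and 10% the arms are equivalent.
- **Relative hazard.** This set is introduced as following the same approach. Above 1.12 (given as 0.95/0.85) the null hypothesis is not rejected. Below 1.0: "If the upper limit is below 1.0, it will be concluded that A is superior to B (at the 20% level". Between 1.0 and 1.12 the arms are equivalent. The hazard is explained as risk of treatment failure in one group relative to the other; neither group is named as numerator.

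The outcome scale changes between sections. The hypotheses in section 3.3 are about cure rates. Section 3.8 opens on failures: "The first outcome variable is the proportion of therapeutic failures in each treatment group". It also says that groups are compared in pairs.

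**The concern.** A higher cure rate is good and a higher failure hazard is bad. A rule that names a winner from the upper limit must therefore swap the arms when the scale changes, unless the contrast itself is reversed. Here the conclusion text is the same on both scales: a low upper limit always favours A. The only stated direction, B compared with A, is attached to the difference rule and nothing replaces it in the survival rule.

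These sentences decide which combination is called superior in a disease that the protocol describes as consistently fatal if untreated. An analyst who follows them literally could declare the arm with more failures superior, or report two conclusions from the same patients that name different arms.

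**Working it through.** **Inputs.** Section 3.3 gives "Assuming a 95% cure rate, a maximum difference in cure rates between the groups of 10"%, "an alpha error of 5% (one-sided test) and a power of 80"%, and 130 patients per group before drop-out. The 130 reproduces with the one-sided two-proportion formula for 95% v 85%:

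- (1.645·√(2·0.90·0.10) + 0.842·√(0.0475 + 0.1275))² / 0.10² = 110.2
- with continuity correction: (110.2/4)·(1 + √(1 + 4/(110.2·0.10)))² = 129.5, so 130
- 130/0.9 = 144.4, so 145

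The sample size is not in question; 130 per arm is used below.

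**Illustration: A 20 failures, B 6 failures, 130 each, so B is better.** The counts are chosen for the example.

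- Failure proportions: 20/130 = 15.4% and 6/130 = 4.6%.
- Difference: 10.8 points. Standard error √(0.154·0.846/130 + 0.046·0.954/130) = 3.66 points. 90% limits: 10.8 ± 1.645·3.66 = 4.7 to 16.8.
- Hazard ratio B/A, assuming proportional hazards and complete follow-up: −ln(1 − 0.046) / −ln(1 − 0.154) = 0.0473/0.1671 = 0.28. Standard error of the log: √(1/20 + 1/6) = 0.465. 90% limits: 0.28·exp(±1.645·0.465) = 0.13 to 0.61.
- Hazard ratio A/B: 3.54, 90% limits 1.64 to 7.60.

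Cure B minus A and failure A minus B are the same number, so three readings of the text remain to be compared:

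| Reading | Difference rule | Survival rule | Result |
|---|---|---|---|
| Cure B−A, hazard B/A | upper 16.8: B | upper 0.61: A | opposite arms named; survival rule wrong |
| Failure B−A, hazard B/A | upper −4.7: A | upper 0.61: A | rules agree; both name the worse arm |
| Failure A−B, hazard A/B | upper 16.8: B | upper 7.60: none named | no conflict |

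**Mirror case: A 6 failures, B 20, so A is better.**

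| Reading | Difference rule | Survival rule | Result |
|---|---|---|---|
| Cure B−A, hazard B/A | upper −4.7: A | upper 7.60: none named | no opposite winner |
| Failure B−A, hazard B/A | upper 16.8: B | upper 7.60: none named | difference rule names the worse arm |
| Failure A−B, hazard A/B | upper −4.7: A | upper 0.61: A | both correct |

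**How often.** In 200,000 simulated trials with 130 per arm, on the first reading, the two rules name opposite arms in about 86% of trials when cure is 85% in A and 95% in B, and in about 64% at 88% v 95%. With the rates exchanged, so that A is better, the figure is about 0.01% or less. With the hazard read A/B it is 0% in all these scenarios.

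**Sign of a carry-over between scales.** The bound 1.12 is 0.95/0.85 = 1.118, a ratio of cure proportions, but the text explains it as a ratio of failure risks. The unswapped superiority sentence fits the same slip.

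**The case against.** The strongest reply is that the numerator of the hazard is never stated, so no reversal can be proved. The difference rule fits failure A minus failure B just as well as cure B minus cure A, and failure is the protocol's own first outcome. With the hazard read A/B, the quoted sentence is correct and all the conclusions fit together. This stands: the contradiction belongs to a reading, not to every reading.

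It also stands that the two complaints, opposite winners and a wrong winner on the failure proportion, come from different readings and cannot both be held at once. And a mislabelled winner could be noticed, since failures are to be given by group and survival curves compared.

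The choice of reference arm in a Cox model is often left to a statistical analysis plan. But this protocol does not leave the matter open: it writes out the conclusions and names the arms. The rescuing convention requires A as the numerator, which turns round the only direction the section states, and nothing in the document supplies it. For the pairs that involve C, the roles of A and B are not assigned at all.

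**Conclusion.** The point holds in this form: section 3.8 ties named winners to confidence limits without stating scale or reference arm, and in the only direction it gives, the survival rule names the arm with more failures. When the arm in the B position is better, the cure-difference rule and the survival rule then name opposite arms, in roughly 64% to 86% of trials for true cure-rate gaps of 7 to 10 points. Those percentages assume 130 evaluable patients per arm, complete follow-up, proportional hazards and Wald intervals.

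Two stronger readings should be resisted. A reader might infer that the text necessarily contradicts itself; it does not, because one unstated convention makes it coherent. A reader might also infer that the worse combination is recommended whenever a real difference exists; when A is better, the hazard rule read B/A generally names no winner. What remains is more than a missing detail, because a written decision rule can endorse the wrong arm, and it should be corrected before any comparison is made.

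**What to change.** In section 3.8, define the contrast once and use it for all three pairs, saying which arm of each pair takes the B position:

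- difference = failure proportion in B minus failure proportion in A;
- hazard ratio = hazard of treatment failure, B versus A;
- upper limit below 0% (or below 1.0): B superior to A;
- lower limit above 0% (or above 1.0): A superior to B.

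Restate the equivalence conclusion on the same scale and direction. Say which conclusion is reported when the lower limit is above 0% and the upper limit is still within the margin, since both could then apply.

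The lower-limit criterion replaces the present conclusion that an upper limit above 10% makes B superior. That is a change of rule, not only of wording, and should be declared as such. The cost is the rewording of one section, with no extra patients or data.

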**4. Data collection**

Data will be collected by medical doctors, clinical officers and nurses involved in the programme. It will be supervised in the field by a medical doctor and by the principal investigator.

**4.1. Laboratory techniques used**

*Test for trypanosomes in the blood:*

WOO: micro-centrifugation in micro-haematocrit tubes (24)

QBC: Quantitative Buffy Coat (if WOO' s test is negative) (25)

*Test for trypanosomes in the lymph node fluid:*

Direct observation of parasites in a wet preparation

*Test for trypanosomes in the CSF:*

Double centrifugation and direct observation in micro-haematocrit tubes (26)

*Spinal cell count:*

In KOVA slides

*Haematology*

Haematocrit

WBC count, total and differential

**4.2. Data to be collected**

*Demographic data:*

Name, age, sex, address, screening method (active or passive).

*Laboratory data on inclusion:*

Result of CATT whole blood and 1/4 dilution

Results of lymph node puncture (trypanosome +/‑)

Results of parasitological examination of the blood (WOO +/‑; QBC +/‑)

Results of parasitological examination of the CSF (trypanosome +/‑)

Spinal cell count

Haematology

*Clinical data on inclusion and during hospitalisation:*

Disease history

Weight/height on admission

Weight on discharge

Temperature

Lymph nodes

Neurological signs

Intercurrent disease

Treatment received and doses

*Side effects of treatment*

*Results of treatment*

*Laboratory data on discharge:*

Results of parasitological examination of the blood (QBC +/‑)

Parasitological examination of the CSF (trypanosome +/‑)

Spinal cell count

Haematology

Specific IgM in CSF and serum (Antwerp)

*Laboratory data during follow-up:*

Results of lymph node puncture (trypanosome +/‑)

Results of parasitological examination of the blood (QBC +/‑)

Parasitological examination of the CSF (trypanosome +/‑)

Spinal cell count

Specific IgM in CSF and serum (Antwerp)

**5. Control of bias and quality control procedures**

**5.1. Bias control**

The randomisation process prevents the introduction of any bias in selection by the care teams when patients are included. However, the lack of blinding does not guarantee uniform treatment of the patients among the 3 groups.

The blocking technique used for the randomisation prevents any imbalance over time in the distribution of the number of patients between the 3 groups that might have been the source of a bias in selection. This process will only be known to the medical personnel at the end of the inclusion period.

Treatment compliance must be guaranteed by the admission of all patients to the treatment centre.

**5.2. Quality control**

A field doctor will be in charge of supervising the study procedures.

## Quality control of the clinical procedures

A written guideline will provide the medical and paramedical staff with all the necessary information for the daily running of the study (inclusion and exclusion criteria, follow-up procedures, etc.). The medical team will receive specific training and the protocol will be tested for one month in the field. The performance of the clinical procedures will be reviewed at regular intervals by the principal investigator.

## Quality control for the laboratory investigations

A code will be allocated to each patient included in the study, which will be used to identify all the laboratory results on inclusion and during follow-up.

The validity of the laboratory measurements will be evaluated periodically on samples taken in duplicate from patients drawn at random and examined blind. In addition, the laboratory measurement instruments will be calibrated regularly throughout the study.

The cell counts in the CSF will be performed twice by the same technician. When the 2 values observed differ by more than 2 cells per mm3, a second person will carry out a third count. The mean of the 3 observed values will be used.

